## Abstract

**Introduction:**

Language and communication difficulties are common across a range of dementias including primary progressive aphasia (PPA). Better Conversations with PPA (BCPPA) is a co-designed communication partner training intervention that aims to improve the experience of conversations for a person with communication difficulties. An NHS-based pilot study of face-to-face BCPPA demonstrated positive outcomes but also raised questions about when and where this intervention should be delivered (at diagnosis or later; face to face and/or remotely), how to best measure the effectiveness of the intervention in line with participant’s priorities and whether BCPPA might be acceptable and useful to people with a range of dementia types. We also had questions about the possible economic implications of BCPPA. In preparation for a future full effectiveness study, the present study will address the following questions:

**Implementation:**

What is the optimal schedule and dosage of BCPPA versus treatment as usual?

**Feasibility:**

What are the eligibility criteria for the BCPPA intervention? Is remote delivery of BCPPA acceptable to people with PPA and other dementias? Can the BCPPA be delivered remotely as intended? Do planned outcome measures show sensitivity to change pre-/post-/3 months post BCPPA? What are the barriers and facilitators to implementation of BCPPA in an NHS setting? What is the most appropriate perspective of analysis and way of measuring costs and outcomes in a future cost-effectiveness analysis of BCPPA versus usual care?

**Methods and analysis:**

In line with Medical Research Council guidance on development and management of complex interventions, Skivington *et al*, 2021 this protocol paper describes a phase II mixed-methods process evaluation and health economic study. This protocol for a randomised controlled pilot feasibility study compares the BCPPA communication partner training intervention with a deferred entry group for people with PPA and other rare dementias and their communication partners. Participants will be recruited at diagnosis and review appointments from two NHS trusts. Participants who have completed a repeated baseline measure will be randomised to either the BCPPA intervention or a deferred entry group. The intervention will be delivered remotely, via teletherapy, over 4–6 weeks depending on goal achievement. The deferred entry group will receive the intervention after a 6-week waiting period, and all participants will be assessed immediately post intervention and again at 3 months post intervention. Outcome measures have been selected in line with the current recommendations for a core outcome set for PPA and to address questions of implementation and health economic evaluation. Qualitative and quantitative analysis methods will be used to explore the data.

**Ethics and dissemination:**

Ethical approval for this study was granted by the Health Research Authority for England and Wales IRAS (Project ID: 341322 REC REF 24-NI-0123). Results from this study will be published in peer-reviewed journal articles and shared with participants and patient and public involvement advisors in accessible formats.

**Trial registration number:**

ISRCTN16268666.

Strengths and limitations of this studyThis study describes a randomised trial exploring the impact of communication partner training interventions for people with dementia.This study employs various outcome measures that were not designed for people with dementia.The co-produced intervention and associated research have been undertaken with guidance from people with lived experience from the very outset.

## Background

 Being able to communicate effectively is fundamental to our daily lives and well-being. When impaired, this has a significant negative impact on quality of life.^1^ Although progressive language difficulty is a common secondary symptom in many dementia types,^2^ primary progressive aphasia (PPA) describes a group of language-led dementias associated with frontotemporal dementia (FTD) or Alzheimer’s disease (AD) in which a progressive difficulty with language is the primary and dominant symptom, affecting all aspects of daily living.^3
4^ Conservatively, approximately 300 000 people are living with PPA in the UK.^5^ In contrast, the burden of AD has been well documented, accounting for 50%–75% of the estimated 990 000 people living with dementia in the UK.^6
7^ Language difficulties are a major contributor to overall disability and reduced quality of life in AD.^8
9^ However, language difficulties in dementias such as AD continue to be under-recognised and under-treated.

The impact of communication difficulties in PPA and AD ripples beyond the person and affects their social and occupational networks. Communication difficulties across all dementia types result in a breakdown in conversational exchanges, whether due to word finding, sentence formulation or more general cognitive impairments.^10^ Communication difficulties carry a high disease burden and are often the primary cause of relationship breakdown.^11^ People with PPA report increasing social isolation, and depression and anxiety are not uncommon.^1^ Spouses of people with PPA report feelings of gradual loss of relationship and meaningful social interaction, as well as the increasing dependency on them to help the person with PPA communicate.^12^ Links between relationship quality and loneliness in dementia have informed recommendations for interventions that help maintain social relationships and thereby help reduce loneliness.^13^ The National Institute for Health and Care Excellence guidelines for dementia research recommendations^14^ and the dementia research roadmap for prevention, diagnosis, intervention and care by 2025^15^ both emphasise as priorities the development and evaluation (including cost-effectiveness) of interventions for people living with dementia and their carers, particularly those focused on everyday functioning and well-being.

The main treatment for communication difficulties in PPA and AD is speech and language therapy. A range of interventions has been developed^16^ to address speech, language and communication difficulties of people with PPA and AD. However, a consensus study that asked people living in the community with dementia what they wanted from non-pharmacological interventions highlighted maintenance of communication and relationships as a key priority.^17^ Similarly, 97 people with PPA and 104 care partners in 15 different countries identified ‘having conversations with families and friends’ as the most important when asked what they most wish to change about their lives.^18^ Specifically, people with PPA and their family members in the UK highlighted a need for interventions to help them feel more skilled in conversations.^19^

Communication partner (CP) training (CPT) represents a range of interventions focused on improving the experience of conversations when one person has a communication difficulty.^20^ Independently of individual linguistic or cognitive communication difficulties, CPT draws on retained strengths, such as gesture, to maintain interactional flow.^13
21–23^ It also focuses on interlocutor behaviour. Some family members use effective strategies such as giving time, but others unwittingly expose their partners’ difficulties through the use of ‘barrier’ behaviours. One example is asking of test questions to which the answer is already known,^24^ a pedagogic behaviour used with children but usually avoided in conversations with peers. CPT interventions aim to reduce conversation barriers and increase the use of effective strategies. This enhances conversational skill and confidence and facilitates the flow of natural conversation, thus reducing social isolation.^25^

A recent systematic review of CPT interventions for people with dementia identified 30 studies that suggest this approach could have positive outcomes.^26^ Better Conversations with Primary Progressive Aphasia (BCPPA) was one of the CPT interventions identified in the review. Using the Medical Research Council framework^27^ and informed by the psychosocial model of dementia, behaviour change theory and conversation analysis, the BCPPA CPT intervention was co-developed with people with PPA and their families.^28^ Prior to delivering BCPPA, the speech and language therapist (SLT) video-records a conversation of the person in a natural everyday conversation with their chosen CP (usually a spouse, family member or friend). The SLT then works through four intervention sessions with the dyad (the person and their CP). First, the SLT facilitates a discussion about how conversation works within the dyad, and the dyad is invited to start reflecting on what they think happens in their conversations before viewing 2–3 clips of their conversations. Then, the SLT assists the dyad to analyse these video recordings to identify what they feel might be barriers (behaviours that create problems in conversation such as ‘test questions’) or facilitators (behaviours that help conversation such as using multi-modal communication—speaking, gesture, drawing and other communication aids). The dyad is supported to set goals to identify which behaviours they wish to do more or less of, followed by practising and problem solving these areas. Finally, the SLT supports the dyad to review their goals and consider any future changes in conversations. Importantly, BCPPA is applicable to all major PPA subtypes yet is tailored to the individual needs of the person and their families.

### Study aims

In line with Medical Research Council guidance on development and management of complex interventions,^27^ this protocol paper describes a phase II mixed-methods randomised controlled pilot and feasibility study with concurrent process and health economic evaluation. The trial will compare the BCPPA CPT intervention to a deferred entry group for people with PPA and other rare dementias and their CPs. In preparation for a future full effectiveness study, the current study will address the following questions:

### Implementation

What is the optimal schedule and dosage of BCPPA vs treatment as usual?

### Feasibility

What are the eligibility criteria for the BCPPA intervention?Is remote delivery of BCPPA acceptable to people with PPA and other dementias?Can the BCPPA be delivered remotely, as intended?Do planned outcome measures show sensitivity to change pre-/post-/3 months post BCPPA?What are the barriers and facilitators to implementation of BCPPA in an NHS setting?What is the optimal sample size for a future effectiveness study?What is the most appropriate analysis and method to measure costs and outcomes in a future trial?

## Methods

### Trial design

This trial was registered retrospectively at ClinicalTrials.gov (ISRCTN16268666). This pilot-feasibility trial employs a randomised controlled design. The protocol follows the Consolidated Standards of Reporting Trials (CONSORT) guidelines, Standard Protocol Items: Recommendations for Interventional Trials (SPIRIT) statement^31^ and the Template for Intervention Description and Replication (TIDieR) checklist and guide.^32^ Comparisons will be made between the treated and the deferred entry groups on pre-treatment versus post-treatment measures. After a 6-week no-treatment phase, deferred participants will then begin intervention. Maintenance will be measured after a 12-week no-treatment period (see figure 1 for an overview of the trial design).

**Figure 1 F1:**
[figure not shown]
Participant flowchart through BCPPA and other rare dementias study. t_x_, Testing timepoints. BCPPA, Better Conversations with Primary Progressive Aphasia; SLT, speech and language therapist.

### Participants and recruitment

#### Setting

Participant dyads will be recruited to the pilot feasibility trial from two NHS sites: a dementia diagnostic clinic (which provides services for people living with dementia in urban and rural areas across England) and an outpatient/community speech and language therapist (SLT) service in the east of England. A research assistant, a qualified SLT at the dementia diagnostic clinic or SLTs at the local collaborators will recruit and screen potential participants.

#### Population

All participants with dementia who are referred to the speech and language therapy services described above will be invited to participate in the study based on the inclusion and exclusion criteria to ensure their eligibility (table 1). All healthcare professionals involved in referral and intervention delivery will be invited to participate in semi-structured interviews to explore perceived barriers and facilitators for future implementation. Fortnightly meetings will be held where potential participants will be discussed on a case-by-case basis to determine eligibility. Inclusion and exclusion will be based on clinical review and participant and CP report.

**Table 1 T1:** Inclusion and exclusion criteria

Inclusion criteria	Exclusion criteria
Participants with dementia*	
Have a diagnosis or possible diagnosis of dementia (eg, PPA, FTD, PCA and AD), as identified by a specialist diagnostic dementia service (informed by case history, neurological examination, brain imaging and appropriate psychometric testing if required) and in line with current diagnostic criteria. Have the ability to communicate and understand communication to participate remotely in the BCPPA programme Can see and hear well enough to participate remotely in the BCPPA programme Are functionally able to engage in a remotely delivered BCPPA programme (ie, able to maintain some concentration and remain in a 60–90 min session with support and minimal challenging behaviour that would be unlikely to cause disruption). English as one of their languages of daily use Have a communication partner (CP; family member or friend) who is able to and consents to participating in the project To be confirmed by the RA or local SLT collaborator at the consent appointment: have access to the internet at home with a minimum download speed of 3.8 Mbps and upload speed of 3 Mbps to support 1080 p HD video for group conference calls. (NB: ideally a download speed of 10–25 Mbps and upload speed of 5 Mbps for best results). A home visit or remote internet speed test and advice session by the RA (or local SLT collaborator where appropriate) will be conducted to test and optimise speeds (eg, by troubleshooting, using cabling and cache flushing). Laptops will be loaned to participants who do not have an appropriate PC or laptop available at home.	Do not have capacity to consent Have a prior history of brain lesions or major head trauma Have major physical illness or disability that could affect participation Present with a major psychiatric diagnosis Present with a prominent behavioural disturbance Present with prominent episodic memory, visual memory or visuo-perceptual impairments that would preclude access to telehealth Are unable to demonstrate as a dyad that they can use a computer (PC, laptop or tablet) to access video conferencing (via Zoom) as observed by their performance on a tech screen at the consent session
Communication partners*	
Having identified a potential participant with dementia who fulfils the inclusion criteria outlined above, their communication partners will also be invited to participate in the study in line with the following criteria: Have been identified by the participant with dementia as a communication partner Can attend the appointments and consent to participating in the study Can see and hear well enough to participate remotely in the BCPPA programme Have English as one of their languages of daily use	Have a diagnosis of dementia. As per routine practice, the researchers will not have access to the medical records of the communication partners, and judgements about inclusion and exclusion will be made based on what potential communication partner participants report to the research team. Are unable to demonstrate as a dyad that they can use a computer (PC, laptop or tablet) to access video conferencing (via Zoom) as observed by their performance on a tech screen at the consent session
Healthcare professionals	
Must have been involved in referring people with dementia to the SLT as potential participants in the study, or they are SLT collaborators who delivered the intervention	None

* Eligibility criteria were dependent on the dyad, rather than on the individual.

AD, Alzheimer's disease; BCPPA, Better Conversations with Primary Progressive Aphasia; CP, communication partner; FTD, frontotemporal dementia; HD, high definition; Mbps, megabits per second; PC, personal computer; PCA, posterior cortical atrophy; PPA, primary progressive aphasia; RA, research assistant; SLT, speech and language therapist.

#### Sample size

Based on pilot study findings^29
33^ and NHS site referral rates, we plan to recruit 36 people with dementia and their CPs (usually a spouse, relative or friend), that is, 72 participants in total over a 12-month period. A previous study provided a conservative sample size calculation of 64 people with PPA (and their CPs) based on scores on the Aphasia Impact Questionnaire.^34^ The current pilot will provide information on recruitment and retention to recruit just over half the above estimated sample size in a relatively brief 12-month period. This will facilitate a sample size calculation for a future full trial of BCPPA using the current outcome measures and with participants representing a wider range of dementia types. Recruitment will be reviewed at 2-month intervals during the study, and the recruitment strategy will be amended as necessary to achieve the target number.

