### Analysis plan

Qualitative and quantitative analysis will be used for this single masked, randomised controlled pilot study. Descriptive statistics will be used to report recruitment, attendance, attrition and reasons for dropout. A CONSORT^59^ and SPIRIT ^60^ flow chart will be used to present overall recruitment to and progression through the study (figure 1). Recorded intervention sessions will be transcribed, and descriptive statistics will be used to analyse dosage. Data collated from potential and actual participants, including date of onset, will also be examined to explore patterns related to optimal dosage and schedule of the intervention. Recruitment and retention rates will be used to support sample size calculations to inform a future full trial and plan the required number of sites to meet this target. Adverse events will also be recorded, and participant interviews examined to inform future recruitment procedures.

All outcome data will be explored to test for assumptions of normalcy. If assumptions are not met, appropriate non-parametric tests will be used. Repeated-measures analyses of variance will be used with group (immediate vs deferred) as a between-subject factor and time (pre-therapy and post-therapy) as a within-subject factor. Results will be used to determine a suitable and sensitive outcome measure and perform a power calculation to determine the sample size for a fully powered trial. Conversation data will be analysed following a procedure developed for the BCA intervention^29^ to identify change in the use of targeted strategies following intervention. This will involve counting barrier and facilitator behaviours in 5 min video samples selected from the pre-intervention and post-intervention conversation samples. These counts will be analysed using Poisson trend tests suitable for observations occurring in Poisson distribution. All pre-therapy conversations will be weighted the same as one another, as will all the post-therapy conversations. Outcomes for different participants will be investigated using a test for homogeneity, and where this is significant, the effect for different dyads will be calculated using the Holm–Bonferroni procedure.

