### Criteria for success

This research will be considered appropriate to proceed to a full effectiveness study if:

The RA, local SLT collaborators and participants report positive views on remote delivery of BCPPA and other rare dementias.Participant recruitment and retention targets are achieved within the designated time frame.An appropriate outcome measure is determined and sample size estimated.An appropriate perspective of analysis and measurement of costs is determined for a future cost-effectiveness analysis.

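### The recruitment progression criterion is a single line at the planned 36 dyads in 12 months with no intermediate outcome, so a pilot recruiting at plan, with no change of strategy, would miss it about half the time

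*Protocol article*

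**What the plan says.** Under Sample size, the protocol article states that "we plan to recruit 36 people with dementia and their CPs", which makes "72 participants in total over a 12-month period". The number is said to rest on pilot findings and on site referral rates; neither is given. Recruitment is to be reviewed every 2 months, and "the recruitment strategy will be amended as necessary to achieve the target number". The Setting section fixes the source: "Participant dyads will be recruited to the pilot feasibility trial from two NHS sites".

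Criteria for success lists four conditions under which a full effectiveness study would be appropriate. The one on recruitment reads "Participant recruitment and retention targets are achieved within the designated time frame". The other three concern views on remote delivery, the choice of outcome measure with a sample size estimate, and the economic perspective. The recruitment condition has no tolerance, lower limit or middle outcome, and the section does not say what follows from a miss.

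Under Analysis plan, "Recruitment and retention rates will be used to support sample size calculations to inform a future full trial", and the same rates are to be used to plan how many sites that trial needs.

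**The concern.** A progression criterion should usually be met when recruitment goes to plan and usually not met when recruitment is clearly too slow. A line placed at the planned count does the second well and the first badly. If the plan is an honest central estimate, chance alone puts the total below the line about as often as above it. A shortfall of one dyad and a shortfall of fifteen then receive the same answer.

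The second issue is what the total means. The protocol expects the strategy to change if recruitment lags. That is sensible management, but a 12-month count reached under two or more strategies is not the rate of any one of them. Site planning for the full trial needs the rate under the strategy that will actually be used.

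**Working it through.** **Inputs from the article.** Target 36 dyads; window 12 months; two sites; review every 2 months. The article's arithmetic is consistent: 2 × 36 = 72 participants, and 36/64 = 56%, which fits its description of the target as just over half of the 64 from an earlier calculation. The planned rate is 36/12 = 3.0 dyads a month, or 36/(2 × 12) = 1.5 per site-month. The 36 itself cannot be reproduced, because the referral rates behind it are not given.

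**Assumption.** Dyads arrive as a Poisson process, so the 12-month count X has mean m = 12 × monthly rate. The article gives no arrival model.

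**Step 1: the line as written, with no strategy change.** The chance of a miss is P(X ≤ 35 | m).

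| True rate (dyads a year) | Reaches 36 | Misses |
|---|---|---|
| 24 | 1.3% | 98.7% |
| 33 | 32.3% | 67.7% |
| 36 (plan) | 52.2% | 47.8% |
| 41 | 80.3% | 19.7% |
| 44 | 90.3% | 9.7% |

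An 80% chance of passing needs an expected 40.9 dyads; 90% needs 43.9. If the yearly rate is itself uncertain around 36 (gamma-distributed, coefficient of variation 0.2 to 0.3), the miss rate is 50.6% to 52.4%. An observed 36 has an exact 95% interval of 25.2 to 49.8 for the yearly rate.

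**Step 2: what an amendment does (illustration only; these rates are assumed).** Start at 2.0 a month and change strategy after month 4 to reach 4.0 a month. The expected total is 4 × 2.0 + 8 × 4.0 = 40, and the chance of reaching 36 is 75.8%, against 1.3% with no change. So amendment lowers the miss rate. With the counts at their expected values over two sites, the rates with exact 95% intervals are:

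- first strategy: 8 dyads in 2 × 4 = 8 site-months, 1.0 per site-month (0.43 to 1.97);
- amended strategy: 32 in 2 × 8 = 16 site-months, 2.0 (1.37 to 2.82);
- pooled: 40 in 24 site-months, 1.67 (1.19 to 2.27).

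The pooled figure describes neither strategy. The period figures are less precise.

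**Step 3: adding a middle band.** Keep 36 or more as proceed; take 27 to 35 as proceed with named changes and under 27 as do not proceed unchanged. The lower limit is 75% of target (0.75 × 36 = 27) and is only an example.

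| True rate (dyads a year) | 36 or more | 27 to 35 | Under 27 |
|---|---|---|---|
| 24 | 1.3% | 28.3% | 70.4% |
| 36 (plan) | 52.2% | 42.7% | 5.1% |
| 41 | 80.3% | 18.9% | 0.8% |

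**Step 4: why not lower the proceed line instead?** Moving it to 29 (80% of target) gives 89.8% at plan, but raises the unqualified pass rate at 24 a year from 1.3% to 17.7%. Keeping 36 and adding the band protects a pilot at plan without making an outright pass easier.

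**The case against.** The case for leaving the text alone has several parts, and much of it stands.

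- **48% is not the failure rate of the protocol's rule.** A reader might infer that it is. It assumes no amendment, whereas the protocol says lagging recruitment will prompt one. It also assumes that true capacity equals the target. Since 36 was set partly from referral rates that are not shown, capacity may be higher, and at 41 a year the miss rate is about 20%. This stands: 48% is a benchmark at one stated rate.
- **A reader might infer that 35 dyads would stop the programme, or that the count alone decides.** The documents do not support either. Recruitment is one of four conditions, the list is introduced by if and not by only if, and no consequence of a miss is given.
- **A reader might infer that a pass reached after amendments is a false pass.** It is not. No research question tests a particular recruitment strategy, and improving recruitment during a pilot and carrying the improvement forward is legitimate. The remaining issue is only which rate to plan from.
- **Other information is collected.** Reasons for ineligibility and refusal are recorded, recruitment is reported descriptively with a flow chart, and a steering group discusses recruitment four times a year. These soften the consequence but do not change the criterion. Reporting by strategy period may be in the full protocol, so its absence from an article is not in itself a fault.

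What is left is the criterion the article does state: one line at the planned value, with nothing between meeting it and missing it.

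**Conclusion.** The point holds in a limited form. The recruitment condition is a single line at the planned number. With Poisson arrivals at exactly the planned rate and an unchanged strategy, it is missed 48% of the time; at a true capacity of 41 a year, about 20%. Amendments reduce the miss rate by an amount that cannot be known in advance, and they turn the 12-month total into a mixture, which matters because recruitment rates are to inform the number of sites.

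The figures rest on the Poisson model and on the assumed true rates; the post-amendment rates are illustrative. The conclusion does not go as far as saying that the plan will wrongly stop this programme or wrongly approve it. The criterion as worded is a weak guide near the target, and a graded version would serve better.

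**What to change.** **Criteria for success.** Keep 36 dyads in 12 months as the proceed outcome. Add a band below it for proceeding with named changes, and a lower limit under which the study does not proceed unchanged. A band of 27 to 35 is an example; the sponsor should set the lower limit and give the reason for it.

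**Analysis plan.** Record the date and content of each change to the recruitment strategy. Report dyads per site-month with an interval for each strategy period. Plan the full trial's sites from the period whose strategy will be carried forward, not from the pooled rate.

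**Cost.** A few sentences in two sections and one descriptive table, with no change to the sample size, eligibility or visits. The downsides are a less clear-cut criterion, a lower limit that needs a judgement, and period-specific rates with wider intervals than the pooled one.
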